## Abstract

**Background:**

Public Health England (PHE) estimates that there are upwards of 160,000 individuals in England and Wales with chronic hepatitis C virus (HCV) infection, but until now only around 100,000 laboratory diagnoses have been reported to PHE and of these 28,000 have been treated. Targeted case-finding in primary care is estimated to be cost-effective; however, there has been no robust randomised controlled trial evidence available of specific interventions. Therefore, this study aims to develop and conduct a complex intervention within primary care and to evaluate this approach using a cluster randomised controlled trial.

**Methods/design:**

A total of 46 general practices in South West England will be randomised in a 1:1 ratio to receive either a complex intervention comprising: educational training on HCV for the practice; poster and leaflet display in the practice waiting rooms to raise awareness and encourage opportunistic testing; a HCV risk prediction algorithm based on information on possible risk markers in the electronic patient record run using Audit + software (BMJ Informatica). The audit will then be used to recall and offer patients a HCV test. Control practices will follow usual care. The effectiveness of the intervention will be measured by comparing number and rates of HCV testing, the number and proportion of patients testing positive, onward referral, rates of specialist assessment and treatment in control and intervention practices. Intervention costs and health service utilisation will be recorded to estimate the NHS cost per new HCV diagnosis and new HCV patient initiating treatment. Longer-term cost-effectiveness of the intervention in improving quality-adjusted life years (QALYs) will be extrapolated using a pre-existing dynamic health economic model. Patients’ and health care workers’ experiences and acceptability of the intervention will be explored through semi-structured qualitative interviews.

**Discussion:**

This trial has the potential to make an important impact on patient care and will provide high-quality evidence to help general practitioners make important decisions on HCV testing and onward referral. If found to be effective and cost-effective the intervention is readily scalable and can be used to support the implementation of NICE recommendations on HCV case-finding.

**Trial registration:**

ISRCTN61788850. Registered on 24 April 2015; Protocol Version: 2.0, 22 May 2015.

**Electronic supplementary material:**

The online version of this article (doi:10.1186/s13063-016-1501-3) contains supplementary material, which is available to authorized users.

## Background

Hepatitis C (HCV) infection is an important contributor to the growing burden of liver disease in the UK [1]. Infection results in cirrhosis and associated life-threatening complications in around 20 % of infected individuals over an average period of 20–30 years [2]. The risk factors for HCV infection include past or current injecting drug use, and being born or having lived in countries with a high prevalence of infection, where infection may have been acquired vertically, or through health care interventions. Approximately 90 % of infections acquired in the UK are among people who inject drugs (PWID) or who have injected drugs in the past [3]. Viral hepatitis, including HCV, is the only major cause of liver disease which is manageable or curable with recently developed therapies, as well as being preventable. HCV case-finding and uptake of treatment [4], however, need to be improved.

The sentinel surveillance of the Hepatitis Annual Report shows that general practice is the single most important setting for HCV testing (30 % of all tests originate here) and for identifying positive patients (31 % of all positive results are generated here). There is limited evidence from a small uncontrolled study in eight practices that targeted case-finding in primary care can increase the proportion of eligible individuals being tested for HCV by a factor of three and the proportion of positive tests amongst individuals tested by a factor of five [5]. The intervention involved offering practice staff training on the epidemiology, diagnosis and management of HCV infection, introducing an electronic patient record search to identify individuals at higher risk of HCV infection, and the offer of a HCV test to higher-risk individuals.

The intervention was used as the basis of a cost-effectiveness model of HCV case-finding in primary care used by the National Institute for Health and Care Excellence (NICE) [6]. Increasing testing in primary care (among those aged 30–54) was cost-effective at an estimated incremental cost-effectiveness ratio (ICER) of £13,900 per quality-adjusted life year (QALY) (79 to 93 % likely to be cost-effective at £20,000 and £30,000 per QALY gained willingness-to-pay thresholds). The intervention was more cost-effective if PWID who had an ongoing risk of transmitting HCV to other people were also tested and treated, and if the baseline testing rate was higher than expected. An additional potential benefit of this approach is that it may also identify patients who had already been diagnosed, but had not been referred for further management, offering an opportunity for reconsideration of such referrals [7].

In the US, a population-based approach has been adopted to identify HCV-infected individuals. Instead of risk-based testing, two individual models were evaluated based on membership of the 1945–1965 birth cohort or the presence of elevated levels of serum alanine aminotransferase (ALT) [8]. The birth cohort strategy was estimated to be cost-effective above a threshold HCV prevalence of 0.53 % which exceeds UK HCV prevalence and so is unlikely to be cost-effective in the UK [9]. ALT screening was previously investigated in a German study where primary care patients with an elevated ALT level of 50–100 IU/l had a HCV prevalence 10-fold above the population prevalence [10]. Since this study, the presence of one of the three significant risk factors for HCV (intravenous drug use, blood transfusion pre 1992 and immigration) or of elevated ALT levels has been shown to diagnose 83 % of unknown HCV-ribonucleic acid (RNA)-positive cases by screening only a quarter of the population studied [11]. The effectiveness of risk-based testing on its own in routine clinical practice is still under much debate. For example, individuals who have occasionally injected drugs in the remote past will probably not seek treatment for injecting drug use. Furthermore, they may be unlikely to disclose their risk status in a consultation with their general practitioner (GP). It has been estimated that from the total population of HCV-infected individuals in a high-income country, only 34 % are easily identifiable in high-risk groups such as a history of being injecting drug users or first-generation migrants [12]. Therefore, the hidden population of HCV-infected individuals may be significant and should be considered when developing future search strategies.

We aim to conduct a complex intervention study in primary care to identify patients who are at higher risk of HCV or patients who have a history of apparently untreated HCV and invite them to undergo testing. We will evaluate this approach using a cluster randomised controlled trial with qualitative and health economic components.

## Methods/design

### Study design

The study will consist of a pragmatic, two-arm, practice-level, cluster randomised controlled trial with a nested qualitative study and economic evaluation.

Ethics approval for the design described here was received from the National Research Ethics Service (NRES) Committee South West-Frenchay (Reference: 15/SW/0094) and research governance approvals obtained across all areas which will be involved in the study. The West of England National Institute for Health Research Clinical Research Network (NIHR CRN) will assist in identifying and accessing GP practices in the South West of England to participate in the trial. Interested practices will be contacted by the trial coordinator who will arrange a meeting with the practice manager, GP partners and practice nurse(s). Since this is a cluster randomised trial, and all patients within one practice will be treated in the same way, consent will be obtained from practices. Patients will not provide individual consent to participate in the intervention, though a purposeful sample will be asked for consent to participate in the nested qualitative study. See Fig. 1 for trial schema.

**Fig. 1 Fig1:**
[figure not shown]
Trial schema and flow diagram

GP practices will be the unit of allocation. Practices will be randomised by an independent statistician in a 1:1 ratio to receive either the intervention or continue care as usual (control group). Randomisation will be stratified by area (Bristol, non-Bristol) and current rate of HCV testing (high: ≥1 % of the practice list versus low: <1 %), and minimised by practice size. In 93 practices in our target area, 15 (16 %) had HCV high testing rates.

### Participant eligibility

#### Qualitative study

Patients must be:Registered with one of the participating intervention practices and offered a HCV testAged 18 years or over, able to provide consent and have access to a telephone

### Sample size

We based our initial sample size calculation on an average practice of 6500; with 4225 adults aged 15–65, we would expect approximately 1 % (42) of people to have an injecting history and in Bristol approximately 40 % (17) of those to have chronic HCV [13]. As a minimum we assume that 10 high-risk patients, based on the algorithm and markers of previous injecting history, will be identified and that the intervention increases uptake of HCV testing from 5 to 17 % of those high-risk patients. Then we require a sample size of 46 practices (23 intervention and 23 control, 230 high-risk patients identified in each arm) to achieve 90 % power at the 5 % significance level. We have assumed an intra-cluster correlation coefficient (ICC) of 0.05, and hence a design effect of 1.45, to accommodate variation in testing rates across practices.

This is a conservative sample size calculation to ensure a large enough number of practices and sufficient power to measure the main intervention effect on uptake of HCV case-finding and diagnosis as well as referral and assessment for treatment. First, practices being approached for the study and identified by the CRN have an average practice list size of 10,000 and, therefore, approximately 6500 adults aged 15–65. Second, it is likely that 2 % of adults will have an injecting history – combining estimates of people currently on opioid substitution treatment and ex-injecting drug users [14, 15]. Third, early pilot studies suggest that it is likely that 80 or more people for an average practice will be identified by the algorithm. This gives approximately 1840 people per arm and substantial power to detect a difference in uptake of HCV testing. In addition, if we assume that two thirds of people diagnosed with chronic HCV attend hepatology for assessment then the case-finding rates of 5 and 17 % convert to HCV treatment readiness rates of 1.3 and 4.4 % and 72 % power (with an ICC of 0.05) to detect a true difference in HCV treatment readiness. As we will adjust the statistical analysis for testing rate and whether a practice is within or outside the Bristol area, this will accommodate some of the clustering, and so it is likely that we will have sufficient power to detect a difference in HCV treatment assessment as well as HCV testing uptake.

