## Appendix

### HCV audit

A HCV test algorithm was developed and piloted at two local general practices before its integration into the Audit + software (BMJ Informatica). The HCV test algorithm was designed to identify registered patients with high-risk HCV markers or patients previously diagnosed who failed to initiate or complete treatment. The search terms included (1) age 18–75 years old, (2) previous intravenous drug use (IDU) history, (3) opiate prescription (including methadone or buprenorphine), (4) opiate misuse, (5) blood transfusion prior to 1991, (6) blood products prior to 1996, (7) transplant prior to 1992, (8) infection with HIV, (9) infection with hepatitis B virus (HBV), (10) born to a mother with HCV, (11) child in care, (12) prison history, (13) altered ALT levels, (14) patients tested for HCV over 1 year previous, before the intervention. Identified individuals considered by GPs to be unsuitable for a discussion about HCV testing or treatment were excluded. Patients also automatically excluded by the HCV audit included (1) patients referred to hepatology, (2) patients tested less than 1 year prior to the intervention, (3) patients receiving end of life/palliative care, and patients with raised ALT levels who have been tested for HCV.

The list of codes are available from the authors and given in Additional file 1. Spirit Checklist also available in Additional file 2.

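### The 72% power for treatment readiness carries a chronic HCV prevalence matching the Bristol injecting-history figure over to the whole audit list, where it is unsupported and probably too high

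*Protocol article*

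**What the plan says.** The Sample size section of the protocol article sizes the trial on testing uptake, supposing that "the intervention increases uptake of HCV testing from 5 to 17 % of those high-risk patients", with 23 practices per arm and an ICC of 0.05. Earlier in the same paragraph it expects about 1% of adults in an average practice to have an injecting history and, in Bristol, about 40% "of those to have chronic HCV".

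The next paragraph moves to a longer list. It expects the algorithm to identify 80 or more people per practice, or about 1840 per arm. It assumes that two thirds of those diagnosed attend hepatology, and says that the uptake rates "convert to HCV treatment readiness rates of" 1.3% and 4.4%, with 72% power at ICC 0.05. Because the analysis will adjust for area and baseline testing rate, which should absorb some of the clustering, it concludes: "so it is likely that we will have sufficient power to detect a difference in HCV treatment assessment as well as HCV testing uptake".

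The list is described elsewhere. Under Planned interventions, one code is enough to be identified. The Appendix (HCV audit) gives the search terms. Besides injecting history and opiate misuse they include opiate prescription, early transfusion, blood products or transplant, HIV, HBV, child in care and prison history, and end with "13) altered ALT levels, (14) patients tested for HCV over 1 year previous, before the intervention". Under Study design, randomisation is stratified into Bristol and non-Bristol practices.

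**The concern.** The conversion names one factor, attendance, but needs a second: the share of tested patients who have chronic HCV. That share is not stated. If it is the 40% quoted for people with an injecting history in Bristol, it has been carried to a broader group, defined by many markers unrelated to injecting and drawn partly from outside Bristol.

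The readiness rates scale directly with this share, so the power depends on it heavily. At stake is how the later steps of the care pathway are read. The protocol says that power for treatment assessment is likely to be sufficient. If it is not, a non-significant result on assessment could be taken as evidence that the intervention does not move patients towards treatment, when the trial had little chance of showing it.

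**Working it through.** **Inputs.** All are from the protocol article, Sample size section, except where marked as assumed.
- Practices per arm: 23. Listed patients per practice: 80. Patients per arm: 23 × 80 = 1840.
- ICC 0.05. Significance level 5%, taken as two-sided because the side is not stated.
- Uptake: 5% control, 17% intervention. Attendance: 2/3.
- Stated readiness rates: 1.3% and 4.4%. Stated power: 72%.
- Chronic HCV prevalence on the audit list: not given, so assumed and shown as a range.

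**Step 1: reproduce the 72%.**
- Design effect = 1 + (80 − 1) × 0.05 = 4.95.
- Effective n per arm = 1840 / 4.95 = 371.7.
- Power for two proportions, with p̄ the mean of the two rates: Φ{[(p2 − p1)√n − 1.96√(2p̄(1 − p̄))] / √(p1(1 − p1) + p2(1 − p2))}.
- With p1 = 0.013, p2 = 0.044 and n = 371.7, power = 0.720. This matches the stated figure, so the 72% does rest on the 80-per-practice list.

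**Step 2: recover the hidden factor.**
- 1.3 / 5 = 0.260; divided by 2/3, this is 0.390.
- 4.4 / 17 = 0.259; divided by 2/3, this is 0.388.
- Forward check with 40%: 5% × 0.40 × 2/3 = 1.33% and 17% × 0.40 × 2/3 = 4.53%. The small gap from 1.3% and 4.4% is consistent with rounding. No other prevalence in the document comes close.

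**Step 3: vary the list prevalence.** Uptake, attendance and 1840 per arm are unchanged. Rates are uptake × prevalence × 2/3. At ICC 0.01 the design effect is 1 + 79 × 0.01 = 1.79.

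| Assumed prevalence | Control rate | Intervention rate | Power, ICC 0.05 | Power, ICC 0.01 |
|---|---|---|---|---|
| 40% | 1.33% | 4.53% | 74% | 99% |
| 30% | 1.00% | 3.40% | 61% | 96% |
| 20% | 0.67% | 2.27% | 44% | 86% |
| 10% | 0.33% | 1.13% | 25% | 57% |
| 5% | 0.17% | 0.57% | 15% | 32% |

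**Step 4: test the adjustment argument at the stated rates (1.3% and 4.4%).**
- ICC 0.04: design effect 4.16, effective n 442.3, power 0.792.
- ICC 0.039: design effect 4.08, effective n 450.9, power 0.800.
- ICC 0.035: design effect 3.765, effective n 488.7, power 0.831.

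So 80% power needs the residual ICC to fall to about 0.039 even if the stated rates are right. The protocol gives no residual ICC after adjustment.

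**Step 5: the primary outcome.** For 5% against 17%, 230 per arm with design effect 1.45 gives an effective n of 158.6 and power of 0.93. With 1840 per arm it is above 0.99. Neither depends on HCV prevalence.

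**The case against.** The strongest reply is that the list may be richer in HCV than its non-injecting codes suggest. The audit also targets people already diagnosed who did not start or complete treatment, and chronic infection in that group would be well above 40%. Injecting history, opiate misuse, substitution prescriptions and birth to a mother with HCV are search terms too. The protocol expects about 2% of roughly 6500 adults, or 130 per practice, to have an injecting history, which is more than the 80 listed. GPs may also remove patients whom they judge unsuitable. The exclusions do not all point one way: dropping recently tested patients removes negatives as well as positives.

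Much of this stands. A reader might infer that prevalence on the list must be below 40%. The documents do not support that, because they do not give the list's composition. They do show that the list is not built as an injecting-history register, and that a Bristol figure would be serving non-Bristol practices as well.

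A second reply is that the protocol openly reports 72%, hedges its conclusion, and may see a smaller ICC after adjustment. That is fair: at ICC 0.01, power is 86% even at 20% prevalence. But that ICC is an assumption made here, and at 10% prevalence it still leaves 57%. Longer lists help little: at ICC 0.05, 160 per practice (design effect 8.95, effective n 411.2) gives 76% at the stated rates.

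Third, the protocol never says that it used 40%. This is an inference from the back-calculation, though no other stated figure fits.

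**Conclusion.** The concern holds as one about an unsupported input. The arithmetic of the 72% is right; a reader might infer a calculation error, and there is none. What fails is the unstated step that gives the whole audit list a prevalence of about 39%, matching only a figure quoted for a narrower group at higher risk. The 72% is therefore probably overstated, and the protocol does not establish that power for treatment assessment is likely to be sufficient.

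The size cannot be fixed from the documents. At the protocol's own ICC of 0.05, power runs from 74% at 40% prevalence to 15% at 5%; at ICC 0.01 it runs from 99% to 32%. These figures assume equal list sizes of 80, two-sided 5% testing, and the stated uptake and attendance.

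A reader might also infer that the trial as a whole is underpowered. It is not: treatment assessment is a secondary outcome, and the number of practices was set on testing uptake. Nor do the documents support a charge that the two power figures were computed inconsistently, since no test is named for either. The low power that would follow from 10 patients per practice is no fault either, because the protocol presents 10 as a minimum and bases the 72% on 80.

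**What to change.** In the Sample size section:

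1. State the chronic HCV prevalence behind the readiness rates of 1.3% and 4.4%, and the population it comes from.
2. Recompute the rates and power with the prevalence expected on the audit list. The two practices in which the algorithm was piloted are the natural source; failing that, show a range of 5% to 40%.
3. Show the power over a stated range of ICC, so that the argument about adjustment rests on a number.
4. Replace the conclusion that power for treatment assessment is likely to be sufficient with the resulting range, and leave the statement for testing uptake as it is.

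The cost is one rewritten paragraph and probably a less favourable figure for a secondary outcome. No extra practices are needed, and neither the design nor the primary analysis changes.

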### Planned interventions

#### Educational training on HCV

Participating practices will be offered a 1-hour educational presentation on HCV and trial procedures, including instructions on how to use the Audit + software (BMJ Informatica), which will be delivered by the trial coordinator at the practice. The practice will also be sent information about free online HCV educational resources (such as the RCGP e-learning module). All staff at the practice will be invited to attend the training session; however, if any members of staff cannot attend the pre-arranged date then the training can be cascaded within the practice.

#### Increasing patient awareness

Posters and leaflets will be displayed in the practice waiting room explaining risk factors for HCV infection. Practices will also be encouraged to include an additional question ‘have you ever injected drugs?’ to the new patient registration proforma. A positive answer would lead to discussion of testing at the next consultation.

#### Identification of patients with risk markers of HCV or patients previously diagnosed

The Audit + software (BMJ Informatica) will be used to assist practices in identifying patients with high-risk HCV markers or patients previously diagnosed who failed to initiate or complete treatment. Audit + is an integrated piece of software which is compatible with multiple GP clinical platforms and will have the HCV test algorithm or ‘audit’ built in. Audit + has been used in previous non-HCV-related studies and shown to reduce the number of patients ‘at risk and unscreened’ by almost two thirds [16]. We selected Audit + because it was becoming familiar to practices and was scalable.

The practice manager will be asked to install the Audit + software onto the practices’ clinical system. Practice staff training will include details on how to install and use the Audit + software as part of the intervention. Within the Audit + software, the HCV audit will be used to identify potentially eligible patients who have pre-defined Read codes defining them as ‘high-risk’ (see Appendix). The Audit + software identifies all patients with one or more of the codes. Patients excluded are those: tested recently for HCV; who have been referred to hepatology; receiving palliative care; who have raised ALT and tested for HCV. The audit will be run and updated every 24 hours on the GP system. GPs will be asked to screen the resultant list at the beginning of the intervention and then regularly, at intervals defined by the practice, to identify new patients during the remainder of the study period. GPs will be permitted to exclude any patient identified by the audit where they feel that an invitation for HCV testing or discussion of treatment is not appropriate. Eligible patients’ records identified by the audit will be automatically flagged by the software to encourage opportunistic testing if the patient attends the surgery. Practice staff can manually switch off the flagging should they feel that the patient is not eligible for a HCV test, if the patient declines a test or if the patient accepts the offer of a test, by entering a specific set of Read codes. Practice staff administrators will also be asked to send out a letter to each patient identified by the audit informing them that the practice is taking part in a study and that they may contact patients by telephone, e-mail or text (whichever is preferred by the practice) to book an appointment to discuss having a test. The patient invitation letters will be automatically processed using the integrated mail-merge facilities built within the software. Diagnosed patients are managed as usual/in standard care at the practice.

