### Control practices

The control practices are only contacted at the time of randomisation and their contribution to the study (collection of data in 12 months’ time) is explained to them at the set-up telephone conversation shortly after they have been randomised. The study team do not contact the control practices again until at the end of the intervention period; control practices will be asked to install and run a ‘dummy version’ of the audit using the Audit + software to search for high-risk HCV patients retrospectively (i.e. the same calendar period as for the intervention practices). These data will be used to compare control and intervention practices to assess the impact of the intervention at the individual patient level as well as at the practice level. At the end of the study period, the control practices will be provided with the software licence for approximately 1 year and can choose to use any of its applications including the HCV audit.

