### Outcome measures and statistical analysis

Data will be collected from three separate sources: general practices (using the Audit + software in the intervention practices and control practices), PHE laboratories Bristol and specialist secondary care hepatology services. During the study period we will also collect data on individuals who, from the practice electronic patient record (age, sex, postcode district, HCV risk factors as included in the algorithm) are identified by the audit as high-risk. As patient consent is not obtained, only anonymous data will be provided for the University of Bristol research team. Therefore, data will be sent by staff at the general practices and secondary care services to a data analyst at PHE laboratories. The data will then be linked using NHS numbers, GP code, name and date of birth, and anonymised and assigned a unique study ID number before sending the data to the research team at the University of Bristol.

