#### Primary outcome measures

*The number and proportion of high-risk patients tested for HCV*. The total number of HCV tests performed at the intervention practices and at the control practices during the intervention period will be collected by PHE laboratories

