#### Secondary outcome measures

The HCV risk factors associated with each patient identified by the audit will be recorded by the Audit + software at participating practices. We will assess:*Number and proportion of high-risk patients testing HCV antibody positive and HCV RNA positive*. The results of each screening HCV test at each of the participating practices will be collected by PHE laboratories. Follow-up tests including polymerase chain reaction (PCR) (which diagnoses chronic HCV) and viral load results will also be collected by PHE laboratories*Number and proportion of high-risk patients referred for specialist assessment*. This will be recorded by data held by PHE laboratories for each of the participating practices*Number and proportion of high-risk patients attending their initial assessment* (*and fibroscan conducted*). This will be obtained from the secondary care hepatology records at University Hospitals Bristol and North Bristol Trusts and sent to PHE laboratories for linkage*Number and proportion of high-risk patients initiating treatment*. These data will be recorded by the secondary care hepatology records at University Hospitals Bristol and North Bristol Trusts and sent to PHE laboratories for linkage

The proportion of high-risk people tested for HCV, compared between intervention and control arms as a rate ratio, will be estimated in a negative binomial regression model, adjusted for whether an individual’s practice is in Bristol or not, and whether that practice has at baseline a high HCV testing rate or not. This regression model accommodates variation in the outcome measure between GP practices. This approach will be adapted to the secondary outcome measures, and also to estimate the risk difference between intervention and control arms for the primary outcome measure. These analyses will follow the intention-to-treat principle, with practices being analysed in the arms to which they are randomised.

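### High-risk patients are identified differently in the two arms after randomisation, and the protocol supports two denominators for the primary proportion, one of which favours the intervention

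*Protocol article*

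**What the plan says.** The primary outcome (Primary outcome measures) is "The number and proportion of high-risk patients tested for HCV". It is compared between arms as a rate ratio, and also as a risk difference. The secondary outcomes are proportions of the same high-risk group.

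How patients come to be counted as high-risk is described in several places:

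- **Intervention arm, GP screening** (Identification of patients with risk markers): "GPs will be permitted to exclude any patient identified by the audit where they feel that an invitation for HCV testing" or discussing treatment would not be suitable. GPs screen the list at the start and then at intervals the practice chooses, "to identify new patients during the remainder of the study period".
- **Appendix, HCV audit:** "Identified individuals considered by GPs to be unsuitable for a discussion about HCV testing or treatment were excluded". The next sentence lists the patients whom the software also excludes automatically.
- **Control arm** (Control practices): at the end of the period, practices run a dummy audit "to search for high-risk HCV patients retrospectively", over the same calendar period. No GP screen is described.
- **Data collection** (Outcome measures and statistical analysis): individual data are gathered on people who "are identified by the audit as high-risk".
- **Health economics:** staff record the time spent screening the high-risk lists and removing ineligible patients. Resource use is extracted at both intervention and control sites for those Audit + identifies as high-risk.
- **Increasing patient awareness:** "Practices will also be encouraged to include an additional question" on past injecting in the new-patient form. Injecting history is an audit search term in the Appendix.
- **Analysis principle** (Secondary outcome measures): "These analyses will follow the intention-to-treat principle, with practices being analysed in the arms to which they are randomised".

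**The concern.** A proportion compared between randomised arms is interpretable only if its denominator is formed by the same rule in both. Here one arm has a judgement-based filter, applied after randomisation by GPs who know their practice's allocation. The other arm has none. A GP who judges an invitation unsuitable is likely to be removing someone who would not have been tested. If those people leave the denominator, the intervention proportion rises without a single extra test.

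A second possible difference is coding. If the registration question or the staff training leads to new risk codes, the intervention list gains patients whom an otherwise identical control practice would not list.

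At stake are the primary rate ratio and risk difference, and every secondary proportion built on the same group.

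**Working it through.** **1. The plan's own figure.** Inputs from Sample size: 5% against 17%, 90% power, 5% significance (two-sided assumed), 10 high-risk patients per practice, ICC 0.05.

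- Design effect = 1 + (10 − 1) × 0.05 = 1.45, as stated.
- Two-proportion sample size with continuity correction = 158 per arm. Then 158 × 1.45 = 229.1, or 22.9 practices, rounded up to 23 practices and 230 patients per arm.

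The stated sample size reproduces and is not in dispute.

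**2. Which denominator?**

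| Place | Are GP-excluded patients counted? |
|---|---|
| Appendix, HCV audit | Can be read as no: GP-judged exclusion stands next to the automatic ones |
| Outcome measures; Secondary outcome measures | Points to yes: data are on patients identified by the audit |
| Health economics | Points to yes: the list is called high-risk before ineligible patients are removed |
| Identification of patients | Open: exclusion may be from invitation only |
| Control practices | No screen described, so all are counted |

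No sentence settles the matter.

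**3. Size if the Appendix is applied.** Assumptions, because the protocol gives no exclusion rate: no true effect, true uptake p = 5% in both arms, a fraction e of the intervention list removed, and those removed untested.

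- Apparent intervention proportion = p / (1 − e); apparent rate ratio = 1 / (1 − e).
- Rejection probability by normal approximation. With m patients per practice and 23 practices per arm, the control variance is p(1 − p)[1 + (m − 1)0.05] / (23m). The intervention variance uses p / (1 − e) for the proportion and m(1 − e) for the cluster size.

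Worked case, e = 20%, m = 80:

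- Intervention proportion 0.05 / 0.8 = 0.0625; difference 0.0125.
- Control variance 0.0475 × 4.95 / 1840 = 0.000128.
- Intervention variance 0.0625 × 0.9375 × 4.15 / 1472 = 0.000165.
- Standard error 0.0171; difference / standard error = 0.73; two-sided rejection probability 11.3%.

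| e | Apparent proportion | Apparent RR | Type I error, m = 10 | Type I error, m = 80 |
|---|---|---|---|---|
| 10% | 5.6% | 1.11 | 5.5% | 6.3% |
| 20% | 6.25% | 1.25 | 7.5% | 11.3% |
| 30% | 7.1% | 1.43 | 11.5% | 22.3% |

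The value 10 is the design minimum; 80 is the figure the protocol takes from early pilot work. If true uptake were 17%, 20% exclusion would show 0.17 / 0.8 = 21.25%, a rate ratio of 4.25 instead of 3.4.

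The bias needs excluded patients to be tested less often than the rest. If they were tested at 5% like everyone else, the proportion would be (0.05 − 0.2 × 0.05) / 0.8 = 5%, with no bias.

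**4. Newly coded patients.** If a fraction a is added to the intervention list and tested at rate t, the proportion is (p + a·t) / (1 + a). With a = 5% (assumed) and p = 5%:

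| t | 0% | 5% | 17% | 50% | 100% |
|---|---|---|---|---|---|
| Apparent RR | 0.95 | 1.00 | 1.11 | 1.43 | 1.90 |

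The direction depends on t, which the protocol does not give.

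**The case against.** The strongest reply is that the protocol already points to a pre-exclusion denominator. Data are collected on patients the audit identifies. The health economics section applies one software-based description to both arms. GP exclusion is tied to whether an invitation or discussion is suitable, which is delivery of the intervention and not membership of the analysis set. Even the Appendix calls the people GPs reject identified individuals, separates them from those the software removes, and uses a past tense that may partly describe the pilot. This stands as far as it goes: loss of GP-excluded patients from the denominator is one reading, not a stated fact. But the Appendix is where the protocol sends the reader for the high-risk definition, and nothing there or elsewhere overrides its exclusion sentence.

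It can also be said that analysis sets belong in an analysis plan. That would answer a missing detail. Here the protocol itself places a one-arm, post-randomisation exclusion in its audit description.

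A reader might further infer that both mechanisms raise the intervention proportion. The text does not support that for coding: the question is only encouraged, it reaches new registrants, and its stated consequence is a discussion, not a Read code. Step 4 shows that the effect could go either way.

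Finally, the exclusion rates are assumed, and treating all excluded patients as untested is the extreme case. Under that formula, reproducing the planned ratio of 3.4 with no true effect would need 1 − 1/3.4 = 71% of the list removed. Exclusion at the rates illustrated could not by itself produce the planned effect.

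**Conclusion.** The concern holds as an unresolved conflict over the primary denominator, combined with identification procedures that differ by arm after randomisation. If the Appendix is applied and excluded patients are tested less often than the rest, the primary proportion is biased towards the intervention. At an assumed 20% exclusion of untested patients the apparent rate ratio is 1.25, and type I error is about 7.5% (10 per practice) to 11% (80 per practice). If all audit-identified patients are retained, this bias is absent and the design figures are unchanged. Intervention-prompted coding is a further possible source of non-comparability, of unknown size and direction.

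A reader might conclude that the intention-to-treat claim fails. It does not: the protocol defines it at practice level, and nothing breaches that. The limit is that analysing practices as randomised does not make the patients counted within them comparable. Nor do the documents show that the comparison is certain to be biased; they leave open a reading under which it would be.

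**What to change.** 1. Reconcile the Identification, Outcome measures, Health economics and Appendix texts with one rule. In both arms, the primary denominator is every patient meeting the automatic audit criteria over the same calendar period. GP-excluded patients stay in, counted as untested unless the laboratory record shows a test, and their number is reported as a process measure. Use the same denominator for the secondary proportions.
2. Add an analysis restricted to patients whose qualifying codes were recorded before a common index date. This removes the effect of intervention-prompted coding. It is an addition and not the primary analysis, because it leaves out the new patients the intervention is meant to find.
3. Add a supportive comparison of total HCV tests per registered patient, from the PHE laboratory counts already collected in both arms, with baseline list size as the offset. It does not depend on the high-risk list. It also counts tests in people outside that group, so it remains supportive.

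GP discretion over whom to invite is unchanged. The cost is a change of wording, one or two extra models on data already collected, and a slightly less favourable reported uptake. The sample size is unaffected.
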